### Timeline

The study recruits all consecutive patients with septic shock at the participating centers who will be prospectively enrolled (Fig. 1). Patient enrollment will coincide with ICU admission, and monitoring along with data recording will continue until hospital discharge will be prospectively enrolled. The study duration will be 12 months from the first IRB approval. Prior to the initiation of the study in September 2024, we anticipate that a minimum of 30 centers will be prepared for inclusion. It is noteworthy that the study is scheduled to commence before securing the majority of Institutional Review Board (IRB) approvals.

**Fig. 1 Fig1:**
[figure not shown]
Protocol flowchart for the EROICASS study. The figure presents a flowchart outlining the key steps and procedures followed in the EROICASS study

Each participating center will enroll consecutive patients over a 120-day window after the IRB approval.

### Data management

#### Data collection

Variables will be recorded upon ICU admission and monitored over 72 h, extending to ICU and hospital discharge. The following codified data will be collected via a collection form:Date, time of ICU admission, and originDemographic data and comorbiditiesAPACHE II score, SAPS II score, and SOFA scoreHemodynamic and perfusion parametersUse of vasopressorsConsciousness assessment (Glasgow Coma Score)Blood chemistry tests (platelet count, bilirubin levels, creatinine levels, azotaemia, potassium, sodium, urine quantity)Renal function and definition of renal damage according to KDIGO criteriaTiming, type, and duration of EBPTTiming, type, and duration of SETSVital status during ICU and hospital stayLong-term outcome post-discharge from ICU

The data will be generated and recorded in participating centers via a web application hosted by SIAARTI using REDCap® software. REDCap provides secure, web-based data capture tools with features including the following:Intuitive interface for validated data captureAudit trails for tracking data manipulation and export proceduresAutomated export procedures for data downloads to statistical packagesData integration and interoperability with external sourcesData will be recorded in the e-CRF using coding procedures to comply with data protection laws, including EU GDPR. Each patient will be assigned a unique subject ID for pseudonymized data analysis.

Access to REDCap will be granted only to data collecting staff of participating centers, adhering to outlined procedures. Unauthorized access is prevented through hierarchical, role-based access concepts. Data management and retention will be overseen by SIAARTI, ensuring secure storage accessible only to system administrators. Each participating center will have access only to the patient data it generated and recorded on the REDCap platform. Periodic ad hoc reports on collected data will be provided by each participating center. Measures for de facto anonymization will be established during data collection and processing, eliminating the need for name-related patient identification.

### Data management and retention

For data management, the study will utilize the REDCap software [11, 12]. The documentation center will not require name-related identification of individual patients at any point during the study. To ensure de facto anonymization during data collection and processing, all necessary measures will be implemented. SIAARTI will oversee data storage, which will be in a secured, central room accessible only to system administrators. Each participating center will be granted access solely to the patient data it has generated and recorded on the REDCap platform. Additionally, each center will be responsible for providing periodic ad hoc reports on the collected data.

### Statistical analysis

#### Sample size

This is a cohort study aimed at determining the cumulative incidence (absolute risk) of EBPT use in septic shock patients. Since no data are available in the literature, we employed a conservative estimate of 50% as the proportion for EBPT utilization in septic shock patients in the ICU to estimate the study sample size. According to Cochran’s formula, we estimated a sample size of at least 97 patients for estimating EBPT utilization with a 95% confidence level and 10% relative precision. If the number of participating centers is sufficient, the study will enroll a maximum of 385 patients to increase accuracy to within 5%.

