#### Outcome measured

##### Primary outcome

Primary outcome is to assess the proportion of EBPT utilization in septic patients.

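### The minimum of 97 patients gives ±10 percentage points absolute, about 20% relative at the planning value of 50%, not the 10% relative precision stated

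*Protocol article*

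**What the plan says.** The primary outcome is a single proportion: "Primary outcome is to assess the proportion of EBPT utilization in septic patients". The Sample size section bases its planning on that proportion. Because the authors know of no literature data, "we employed a conservative estimate of 50% as the proportion for EBPT utilization in septic shock patients in the ICU".

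Two targets follow:

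- **Minimum:** "we estimated a sample size of at least 97 patients for estimating EBPT utilization with a 95% confidence level and 10% relative precision".
- **Maximum**, conditional on enough centres taking part: "the study will enroll a maximum of 385 patients to increase accuracy to within 5" per cent.

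The first margin is expressly called relative. The second carries no scale. Nothing elsewhere in the article redefines either margin or gives another anticipated proportion.

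**The concern.** An absolute margin is counted in percentage points. A relative margin is a fraction of the proportion being estimated. At 50% they differ by a factor of two: 10% relative is ±5 points, while 10% absolute is ±10 points. Since the required number of patients varies with the inverse square of the margin, the choice of scale changes it fourfold.

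The figure of 97 is familiar as the Cochran result for ±10 points absolute, so the word relative looked wrong. This section is the only precision justification given for the primary outcome, and 97 is a number at which the study may stop. A reader who takes the text literally would expect a 95% interval of about 45% to 55% if half the patients receive EBPT. The design would give about 40% to 60%.

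**Working it through.** **Inputs**, all from the Sample size section: p = 0.50; 95% confidence, two-sided, so z = 1.96 and z² = 3.8415; minimum n = 97 with a stated 10% relative margin; maximum n = 385 with a 5% margin of unstated scale.

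**Formula.** For an absolute half-width d, n = z² p(1 − p)/d². For a relative half-width e, put d = e·p, which gives n = z² (1 − p)/(p e²).

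**Reproducing the plan's figures at p = 0.50**

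- Absolute, d = 0.10: 3.8415 × 0.25 / 0.01 = 96.04, rounded up to **97**. This matches the stated minimum.
- Absolute, d = 0.05: 3.8415 × 0.25 / 0.0025 = 384.15, rounded up to **385**. This matches the stated maximum.

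**Taking the relative label literally at p = 0.50**

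- e = 0.10, so d = 0.10 × 0.50 = 0.05: n = 384.15, rounded up to **385**, not 97.
- e = 0.05, so d = 0.025: 3.8415 × 0.25 / 0.000625 = 1536.6, rounded up to **1537**, not 385.
- A one-sided z of 1.645 does not rescue the stated minimum: with d = 0.05 it gives 270.6, or 271.

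**Precision delivered at p = 0.50**

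| n | Absolute half-width | Relative half-width |
|---|---|---|
| 97 | 1.96 × √(0.25/97) = 0.0995 | 0.0995/0.50 = 19.9% |
| 385 | 1.96 × √(0.25/385) = 0.0499 | 0.0499/0.50 = 10.0% |

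**Could both margins be relative at some other p?** At p = 0.80, e = 0.10 gives 3.8415 × 0.20 / (0.80 × 0.01) = 96.04, or 97, and e = 0.05 gives 385. That reading contradicts the stated 50%.

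**Is 50% conservative?** For absolute precision, yes, because p(1 − p) is largest at 0.50. For relative precision, (1 − p)/p grows as p falls. The documents do not give the true utilization, so the proportions below 0.50 are an assumed range:

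| p | n for 10% relative | Relative half-width with n = 97 |
|---|---|---|
| 0.5 | 385 | 19.9% |
| 0.3 | 897 | 30.4% |
| 0.2 | 1537 | 39.8% |
| 0.1 | 3458 | 59.7% |

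**The case against.** The best defence is that this is one wrong adjective. The formula, the 50%, the confidence level and both sample sizes agree with each other on the absolute scale. The pairing of 97 with 10% and 385 with 5% lets a statistician see what was done. No patient numbers change, and the Statistical analysis plan section commits to reporting utilization with 95% confidence limits, so the precision achieved will be visible. That all stands, and it is why the remedy is confined to wording. It does not make the stated precision right: the text makes an explicit claim that its own inputs contradict.

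A second point is that 97 is only a floor. The Timeline section expects at least 30 centres, each enrolling for 120 days; 97 patients would be about 3 per centre (97/30 = 3.2) and 385 about 13 (385/30 = 12.8). If 385 are enrolled, 10% relative precision is met at p = 0.50. This is fair, but accrual is not known in advance, and the text ties the 10% relative claim to the minimum, not the maximum.

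Third, the relative label is attached only to the 10%, so the figure of 1537 for 5% relative answers a claim the protocol does not make outright. Likewise, the point about 50% not being conservative disappears once the label is corrected. Both are accepted as far as they go. The 5% is unlabelled rather than mislabelled, but following directly after a relative margin it invites the same reading, so it needs its own label. The lower-proportion figures show what the text implies as it stands; they are not proposed sample sizes.

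**Conclusion.** The stated precision for the minimum sample is wrong. Under the plan's own inputs, 97 patients give ±10 percentage points absolute, which is about 20% relative: twice the margin claimed. Meeting 10% relative precision at 50% would take 385 patients, about four times the minimum. The sample-size arithmetic is sound; the scale attached to it is not. Both targets are correct as absolute margins of 10 and 5 points, and 50% is conservative on that scale alone.

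The factor of two holds at p = 0.50. For lower proportions the shortfall against 10% relative is larger, and it closes only at about p = 0.80. The figures use the normal approximation and treat patients as a simple random sample, with no allowance for clustering by centre.

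**What to change.** In the Sample size section, replace the relative-precision wording for 97 patients with an absolute precision of ±10 percentage points (95% confidence interval half-width). State the precision for 385 patients as ±5 percentage points absolute. Add that 50% is the worst case for absolute precision only.

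This costs one or two sentences and no additional patients; the stated precision becomes less favourable. If the sponsor did intend 10% relative precision, rewording is not enough: the minimum would have to rise to 385 at an assumed 50%, and to more if utilization were expected to be lower.

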### Statistical analysis plan

All parameters will be described by frequencies (absolute and relative) and mean (SD) or median (IQR) based on data distribution. EBPT and SETS will be described in terms of indication, modality, and timing. Differences between patients undergoing and not undergoing EBPT will be assessed using the chi-square test (for discrete variables) or Student’s *T*-test (for continuous variables). Continuous variables not normally distributed will be compared using appropriate nonparametric tests (such as Wilcoxon’s sign test). Similar tests will be conducted to compare patients alive at discharge (from ICU and from hospital) versus those who did not survive, as well as patients with and without AKI (according to KDIGO criteria).

For patients undergoing EBPT or SETS, paired tests (paired *t*-test, Wilcoxon signed-rank test) will be applied to assess statistical differences in lactates, VIS, SOFA score, and AKI stage (based on KDIGO criteria) before and after EBPT or SETS. Multivariable generalized linear regression models will be performed to investigate the association between clinical outcomes (renal outcomes, mortality, ICU and hospital length of stay, free days from EBPT or SETS) and demographic/clinical variables in patients undergoing EBPT or SETS. Depending on the number of participating centers, the characteristics of the centers collected in the case report form may be included in the list of predictor variables for the models.

Relationships will also be analyzed using survival analysis (Kaplan–Meier approach and Cox proportional hazard models) to account for failure time and censoring data. EBPT utilization will be reported in terms of absolute risk and 95% confidence levels. Absolute risk will also be estimated for patients with and without AKI. Estimates will be used to assess the risk ratio for mortality (at 28 days and 90 days) in the entire population and stratified according to the presence or absence of AKI. The same approach will be used to assess SETS utilization in the ICU. All hypothesis tests will be two-sided, and *P* < 0.05 will be considered to indicate statistical significance.

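### Student's t-test is named for unpaired comparisons of self-formed groups with no provision for unequal variance; if group sizes and SDs both differ, its type I error departs from 5%

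*Protocol article*

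**What the plan says.** The relevant text is in the section Statistical analysis plan of the protocol article.

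- **Comparison and test.** "Differences between patients undergoing and not undergoing EBPT will be assessed using the" "chi-square test (for discrete variables) or Student’s" t-test, the latter for continuous variables. The sentence does not say whether variances are pooled.
- **Fallback.** "Continuous variables not normally distributed will be compared using appropriate nonparametric tests". The trigger is the shape of the distribution; unequal variance is not mentioned.
- **Extension.** "Similar tests will be conducted to compare patients alive at discharge" (ICU and hospital) with those who died, and patients with and without AKI.
- **Error rate.** "All hypothesis tests will be two-sided", with significance at P < 0.05.

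The section Sample size gives the only figure for the EBPT split: "we employed a conservative estimate of 50% as the proportion for EBPT utilization in septic shock patients". It is adopted because no data were available. The Abstract and the Background say that 28-day mortality may reach 40%. No SD of any variable is given.

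**The concern.** Student's test, named without qualification, is by convention the pooled-variance test. It holds its nominal error rate when the two groups are equal in size or equal in spread. It need not do so when both differ.

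In this non-interventional cohort the groups are defined by treatment choice, by death or by organ failure, so nothing in the design secures equal size or equal spread. If the smaller group is the more variable one, differences are declared significant too often. If it is the less variable one, they are declared too rarely. The normality-based fallback does not catch a variable that is roughly normal in both groups but has different SDs. At stake is whether the stated 5% applies to these secondary comparisons.

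**Working it through.** **Inputs from the document.** Two-sided 5% (Statistical analysis plan); N = 97 to 385 and a 50% EBPT share (Sample size); 28-day mortality up to 40% (Background), which suggests about 40:60 as a rough guide for the survivor comparison.

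**Assumptions, not in the document.** SD ratio r (smaller group over larger group) from 0.5 to 2; splits of 30:70 and 20:80; normal data with equal means.

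**The plan's own figures first.** Cochran's formula is n = z²p(1−p)/e² with z = 1.96 and p = 0.50.
- e = 0.10: 3.8415 × 0.25 / 0.01 = 96.04, rounded up to 97.
- e = 0.05: 3.8415 × 0.25 / 0.0025 = 384.15, rounded up to 385.

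Both sizes reproduce with e read as absolute precision. They concern the primary proportion. For the t-test the plan states only the nominal 5%.

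**Large-sample error of the pooled test.** Let f be the smaller group's share. The ratio of the variance that Student's test assumes for the mean difference to its true variance is

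R = (f·r² + 1 − f) / ((1 − f)·r² + f),

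and the actual type I error is 2[1 − Φ(1.96·√R)]. If f = 0.5 or r = 1, then R = 1 and the error is 5%. Both conditions must fail before the error moves.

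**Results.** The last column gives simulated values for Student's test (200,000 replicates per setting).

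| Split | r | R | Formula | Simulated, N = 97 / 385 |
|---|---|---|---|---|
| 50:50 | 0.5 to 2 | 1 | 5.0% | 4.9–5.2% / 5.0–5.1% |
| 40:60 | 0.5 | 0.700/0.550 = 1.273 | 2.7% | 2.8% / 2.7% |
| 40:60 | 1.5 | 1.500/1.750 = 0.857 | 7.0% | 7.0% / 6.9% |
| 40:60 | 2 | 2.200/2.800 = 0.786 | 8.2% | 8.3% / 8.4% |
| 30:70 | 0.5 | 0.775/0.475 = 1.632 | 1.2% | 1.2% / 1.3% |
| 30:70 | 1.5 | 1.375/1.875 = 0.733 | 9.3% | 9.3% / 9.3% |
| 30:70 | 2 | 1.900/3.100 = 0.613 | 12.5% | 12.7% / 12.5% |
| 20:80 | 0.5 | 0.850/0.400 = 2.125 | 0.4% | 0.4% / 0.5% |
| 20:80 | 1.5 | 1.250/2.000 = 0.625 | 12.1% | 12.3% / 12.1% |
| 20:80 | 2 | 1.600/3.400 = 0.471 | 17.9% | 18.4% / 18.0% |

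Two checks on these results:
- At 40:60, as r grows without limit, R tends to 0.4/0.6 = 0.667 and the error only to about 11%.
- R does not depend on N, so enrolling 385 rather than 97 patients does not remove the effect.

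**With the change.** Welch's test gave 4.9% to 5.2% in every simulated setting (smaller group 10% to 50% of N, r from 0.5 to 2, both sample sizes).

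**The case against.** The strongest case against the point has four parts.

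1. **No imbalance or unequal spread is documented.** At the plan's own 50% EBPT share the error stays at about 5% for every SD ratio considered. This stands as a limit on the size of the point. It does not remove the point, because the 50% was chosen for lack of data and is not a forecast. The AKI split and the discharge-survival splits are not given at all.
2. **The variance form may be a detail left to a fuller plan.** The article does not say that variances are pooled, and a fuller plan could specify otherwise. This stands in part. Still, the article names a test, and under the usual reading that name means the pooled one, so the comment is on a stated method and not on an omission.
3. **Little depends on this test.** The primary outcome is a proportion with a confidence interval. Mortality is handled by risk ratios, Kaplan–Meier and Cox models, and other clinical outcomes by regression. This stands.
4. **Only roughly normal variables are concerned.** The others go to nonparametric tests. This also stands.

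A reader might infer that unequal group sizes alone make the error two to three times the stated 5%. The documents do not support that. With equal SDs the error is 5% at any split. A two- to threefold rise needs, for example, 30:70 with an SD ratio of 2 or 20:80 with a ratio of 1.5, with the larger SD in the smaller group. None of these values is in the documents. At 40:60, the only other split they hint at, the error is at most about 8.4% for SD ratios up to 2. That 40% is also 28-day mortality, not death by ICU or hospital discharge.

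**Conclusion.** The point holds as a minor improvement. The plan names a test whose stated 5% depends on equal group sizes or equal SDs, applies it to groups where neither is assured, and has no safeguard against unequal variance. The departure from 5% is conditional: none at 50:50, modest at 40:60, and material only if a split of about 30:70 or more uneven coincides with clearly different SDs. It can go in either direction.

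These sizes rest on assumed splits and SD ratios, on normal data, and on reading Student's test as the pooled one. The estimate of EBPT use and the planned sample size are untouched.

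**What to change.** In the Statistical analysis plan, replace Student's t-test for the unpaired comparisons (EBPT versus none, survivors versus non-survivors, AKI versus no AKI) with Welch's unequal-variance t-test. Use it throughout, without a preliminary test of equal variances, and report the mean difference with its Welch 95% CI. The paired tests for before-and-after changes stay as they are.

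The cost is one changed term and a software option. No extra data or patients are needed. When variances are equal, both tests estimate the same standard error and Welch's only gives up some degrees of freedom, so the loss of power is negligible.

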### Setting

All consecutive patients with septic shock at the participating centers will be prospectively enrolled. Patient enrollment will coincide with ICU admission, and monitoring along with data recording will continue until hospital discharge. This study is observational in nature; enrolled patients will not receive additional treatments beyond those routinely administered in the ICU. All clinical parameters, including those associated with EBPT treatment, will be documented in the web-based CRF.

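### The only nonparametric test named for comparing unmatched groups, Wilcoxon's sign test, is a paired procedure; the rank-sum test should be named instead

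*Protocol article*

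**What the plan says.** All the relevant text is in the Statistical analysis plan section of the Protocol article.

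- The first comparison is between patients with and without EBPT: "Differences between patients undergoing and not undergoing EBPT will be assessed using the chi-square test (for discrete variables) or Student’s *T*-test (for continuous variables".
- The next sentence gives the fallback for non-normal continuous variables: "Continuous variables not normally distributed will be compared using appropriate nonparametric tests (such as Wilcoxon’s sign test".
- The same approach is extended to outcome groups, "Similar tests will be conducted to compare patients alive at discharge (from ICU and from hospital) versus those who did not survive", and to renal groups, "as well as patients with and without AKI (according to KDIGO criteria".
- The following paragraph treats within-patient change separately: "paired tests (paired *t*-test, Wilcoxon signed-rank test) will be applied to assess statistical differences in lactates, VIS, SOFA score, and AKI stage".

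The Setting section describes the cohort as consecutive: "All consecutive patients with septic shock at the participating centers will be prospectively enrolled". No matching is described, and neither the rank-sum nor the Mann–Whitney test is named anywhere in the article.

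**The concern.** Each of the three contrasts compares one set of patients with another, and nothing links a patient in one group to a patient in the other. The parametric test named for the first contrast, Student's t-test, is a test for independent groups. The only nonparametric example beside it belongs to the paired family.

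The name Wilcoxon's sign test is not standard. It blends the sign test and the Wilcoxon signed-rank test. Both work on one difference per pair, so the mismatch is the same under either reading.

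Taken literally, the instruction leaves the analyst two courses. One is to invent pairs, in which case the p-value depends on the pairing chosen. The other is to use a different test from the one named, which leaves the published plan and the report out of step.

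**Working it through.** **1. Design against test.**

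| Comparison | Same patients in both arms? | Nonparametric test named | Fits? |
|---|---|---|---|
| EBPT vs no EBPT | No | Wilcoxon's sign test | No |
| Survivors vs non-survivors | No | Similar tests | No |
| AKI vs no AKI | No | Similar tests | No |
| Before vs after EBPT or SETS | Yes | Wilcoxon signed-rank | Yes |

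The sign test counts how many of m paired differences d = y − x are positive and refers the count to a binomial(m, 0.5). The signed-rank test ranks the absolute values of the same differences. The rank-sum test ranks all n1 + n2 observations together and needs no pairs. Only the last suits the first three rows.

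**2. Does any stated figure depend on this?** The article's computed figures are the two sample sizes in the Sample size section. With p = 0.5, z = 1.96 and d taken as an absolute half-width, Cochran's formula n = z²p(1 − p)/d² gives:

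- d = 0.10: 3.8416 × 0.25 / 0.01 = 96.04, rounded up to 97.
- d = 0.05: 3.8416 × 0.25 / 0.0025 = 384.16, rounded up to 385.

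Both match the article and neither involves the test in question.

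**3. What forced pairing would cost (illustration).** The total of 97 is the article's minimum. Everything else is assumed: lognormal data with log-SD 1, a log-shift of 0 (null) or 0.6 (alternative), three possible splits, and 3000 simulated data sets per cell. Each patient in the smaller group was paired arbitrarily with one in the larger group, and the rest were dropped. The two-sided level was 0.05.

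| Split | Patients dropped | Power: rank-sum | Power: forced sign | Power: forced signed-rank | Type I error, same order |
|---|---|---|---|---|---|
| 49/48 | 1 | 0.82 | 0.54 | 0.76 | 0.046 / 0.025 / 0.048 |
| 68/29 | 39 | 0.73 | 0.32 | 0.52 | 0.046 / 0.025 / 0.049 |
| 87/10 | 77 | 0.40 | 0.09 | 0.20 | 0.044 / 0.026 / 0.052 |

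The Monte Carlo standard error is at most √(0.25/3000) ≈ 0.009. Forced pairing loses power at every split, and more as the groups become less equal. It does not raise the false-positive rate.

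**4. Dependence on the pairing.** In one simulated 68/29 data set (assumed log-shift 0.5) the rank-sum p-value was 0.017. The sign test was then run on 2000 random pairings of the same data. Its p-values had a median of 0.14, and the central 95% ran from 0.002 to 1.0. The same data could therefore be reported as significant or not according to the pairing drawn.

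**The case against.** The plan does not bind itself to the named test. It asks for appropriate nonparametric tests and offers this one as an example, so an analyst who used the rank-sum test would comply. The next paragraph reserves paired tests for before/after data under the standard name, which suggests that the authors know the difference and that the earlier name is a slip for rank-sum. With unequal groups a paired routine cannot be run without first discarding patients, so the slip would very likely be noticed. This argument stands as to weight. It does not remove the error, because the one example given is not an appropriate test for these comparisons and nothing else in the article corrects it.

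A reader might infer more than the text supports:

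- *That the plan intends to pair unrelated patients.* Nothing in the article suggests this.
- *That the p-values would be meaningless or the false-positive rate inflated.* In the simulation the type I error stayed at or below about 0.05. The costs were lost power and dependence on the pairing.
- *That most continuous comparisons would be affected.* The article does not say which variables enter the group comparisons or which will prove non-normal. Lactate, VIS and SOFA are explicitly assigned to the before/after analysis, where the signed-rank test is a proper choice, and length of stay to the regression models.
- *That the groups are known to be unequal.* No group sizes are given, and the planning proportion of 50% would make the EBPT groups about equal. Unequal groups are likely in practice but are an expectation. Even equal groups would not supply pairs.

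**Conclusion.** The point holds as a correction of limited weight. As written, the only nonparametric test named for three independent-group contrasts is a one-sample or paired procedure that does not apply to them.

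Its reach is confined to secondary univariable comparisons of non-normal continuous variables. The primary outcome is a proportion reported with a 95% confidence interval. The sample size rests on that proportion. The mortality associations use risk ratios, Kaplan–Meier curves and Cox models. None of these changes.

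The conclusion about the test needs no numerical assumption, only that the groups are unmatched, as the article describes them. The power figures illustrate the size of the loss under assumed data and splits; they do not predict what this study would see. The realistic harm is an ambiguous prespecified method and an unexplained departure from it at analysis, rather than wrong published results.

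**What to change.** In the Statistical analysis plan section, replace Wilcoxon's sign test with the Wilcoxon rank-sum (Mann–Whitney U) test for the comparisons of EBPT versus no EBPT, survivors versus non-survivors, and AKI versus no AKI. Keep the Wilcoxon signed-rank test only for the before/after EBPT or SETS comparisons, where it is already named. If a separate full analysis plan exists, check that it carries the same wording.

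The cost is one phrase. No sample size, outcome definition or data collection item changes, and the correction has no statistical downside.
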